## Abstract

**Background:**

People with serious mental health problems (SMHP) are more likely to be admitted to psychiatric hospital following contact with crisis services. Admissions can have significant personal costs, be traumatic and are the most expensive form of mental health care. There is an urgent need for treatments to reduce suicidal thoughts and behaviours and reduce avoidable psychiatric admissions.

**Methods:**

A multi-stage, multi-arm (MAMS) randomised controlled trial (RCT) with four arms conducted over two stages to determine the clinical and cost effectiveness of three psychosocial treatments, compared to treatment as usual (TAU), for people with SMHP who have had recent suicidal crisis. Primary outcome is any psychiatric hospital admissions over a 6-month period. We will assess the impact on suicidal thoughts and behaviour, hope, recovery, anxiety and depression. The remote treatments delivered over 3 months are structured peer support (PREVAIL); a safety planning approach (SAFETEL) delivered by assistant psychologists; and a CBT-based suicide prevention app accessed via a smartphone (BrighterSide). Recruitment is at five UK sites. Stage 1 includes an internal pilot with a priori progression criteria. In stage 1, the randomisation ratio was 1:1:1:2 in favour of TAU. This has been amended to 2:2:3 in favour of TAU following an unplanned change to remove the BrighterSide arm following the release of efficacy data from an independent RCT. Randomisation is via an independent remote web-based randomisation system using randomly permuted blocks, stratified by site. An interim analysis will be performed using data from the first 385 participants from PREVAIL, SAFETEL and TAU with outcome data at 6 months. If one arm is dropped for lack of benefit in stage 2, the allocation ratio of future participants will be 1:1. The expected total sample size is 1064 participants (1118 inclusive of BrighterSide participants).

**Discussion:**

There is a need for evidence-based interventions to reduce psychiatric admissions, via reduction of suicidality. Our focus on remote delivery of established brief psychosocial interventions, utilisation of different modalities of delivery that can provide sustainable and scalable solutions, which are also suitable for a pandemic or national crisis context, will significantly advance treatment options.

**Trial registration:**

ISRCTN33079589. Registered on June 20, 2022.

**Supplementary Information:**

The online version contains supplementary material available at 10.1186/s13063-024-08293-5.

## Introduction

### Background and rationale

In the United Kingdom (UK), psychiatric inpatient care has seen a sustained rise following the COVID-19 pandemic and from increased socio-economic deprivation [1]. In England, a compulsory admission under the Mental Health Act 2007 (formerly Mental Health Act 1983) is mandatory in cases of considerable danger to self, including suicidal ideation [2]. The rates of compulsory admissions have continued to increase each year in the UK [3]. Yet, psychiatric hospital admissions (PHAs) can have significant personal costs such as stigma, loss of relationships, employment and housing, and traumatisation [4, 5]. PHAs are the most expensive form of mental health care with the estimated costs of involuntary psychiatric admissions in the UK totalling £6.8 billion [6]. A psychiatric admission is often seen as an unacceptable form of care to patients as it represents a restriction on personal freedom and wards are not always safe, therapeutic or conducive to recovery [4]. The UK National Health Service (NHS) acknowledges that significant improvement is required to ensure inpatient settings are therapeutic [7].

Patients with serious mental health problems (SMHPs) have an elevated risk of physical health comorbidities, i.e. cardiovascular and metabolic health conditions [8], and the COVID-19 pandemic introduced a new challenge for vulnerable patients and service providers due to the increased risk of transmission in a ward environment [9]. There is already a large and discriminatory mortality gap for those with an SMHP diagnosis, with those who experience psychosis, on average, living 15 years less in comparison to people without a psychosis diagnosis [10]. Such elevated risk in the context of an epidemic or pandemic for those who are a psychiatric inpatient is of concern.

Crisis teams are part of a UK strategy to provide community care to people with SMHPs who are experiencing a suicidal crisis with the aim of reducing PHAs [11]. However, more than half of the crisis team patients have an admission within a year of discharge from hospital [12]. People with an SMHP diagnosis, such as psychosis, bipolar and emotionally unstable personality disorder (EUPD), are the diagnostic groups most likely to have an admission following contact with a crisis team [13] and the majority of first admissions are due to suicidality [14]. Strategies to reduce PHAs include crisis planning, self/symptom management, relapse prevention and monitoring of suicidal risk [15]. Of these, interventions that focus on symptom management, relapse prevention and patient functioning can reduce the average number of readmissions [16]. However, the methodological limitations to existing studies, including risk of bias and inconsistent results, suggest that a high-quality trial of self-management strategies with admissions as the primary outcomes is required [16].

It is a deeply concerning fact that one in 100 deaths are by suicide and that over 700,000 people die per year because of suicide [17]. This has far-reaching emotional, social and economic impacts and it is crucial to have an evidence base for interventions that support people in a crisis to prevent suicide. Interventions that are designed to reduce suicidal ideation and behaviour may have also have an indirect effect on reducing admissions given the majority of first admissions occur in response to a suicidal crisis [14].

A recent network meta-analysis reports that dialectical behaviour therapy (DBT), brief intervention and contact (BIC) and cognitive therapy (CT) were superior when compared to treatment as usual (TAU) in preventing suicide attempts [18]. Whilst these interventions show promise to reduce suicide attempts, the authors conclude that further research is needed to validate which interventions are most effective and to our knowledge it is unclear whether there is an indirect effect on PHAs. One brief intervention and contact approach delivered remotely, with telephone follow-up support, is SAFETEL [19]. This intervention incorporates a safety planning approach with identification of warning signs, distraction techniques and social/professional support sources with follow-up telephone support and has its origins in CT for suicidality. This approach has been shown to be both safe and acceptable for people in the UK who have presented to emergency departments after a suicide attempt [20]. Digital interventions have been proposed to improve access to treatment for people who are at risk of suicide and have the potential to extend the scalability and accessibility of an intervention [21]. A review of the evidence regarding digital cognitive behavioural therapy (CBT) showed that those who received digital CBT had a significant reduction on suicidal ideation scores in comparison to a control group, but did not show a significant effect for suicide attempts and that human support with completion was required to increase engagement with a digital intervention [22]. One digital CBT intervention included in the review which showed initial promise for reducing suicidal thinking is an online self-guided programme for adults designed to help reduce suicidal ideation (Living with Deadly Thoughts: LwDT) [23]. LwDT was further developed from a web-based intervention into a smartphone app version to improve access (BrighterSide smartphone app) with considerable input from people with lived experience of suicidal thinking and behaviours [24]. One brief, psychosocial approach that incorporates strategies derived from BIC and motivational interviewing with peer support (PS) is PREVAIL (Peers for Valued Living), which has demonstrated feasibility and acceptability for patients at high risk of suicide [25]. PS is highly valued by service users, forming part of the vision for the future of mental health services [26] and is associated with positive effects on measures of hope [27], which protects against suicidal ideation [28]. As outlined, these three candidate interventions have demonstrated feasibility and acceptability and are deliverable remotely, which may increase scalability if effective and future proof intervention delivery in the context of an epidemic, pandemic or other crises.

In summary, there is a need to prevent avoidable PHAs for people who have SMHP. There is strong theoretical evidence to suggest that interventions which target suicidal ideation and behaviour can reduce avoidable admissions, since many admissions are because of a suicidal crisis. The Remote Approaches to Psychosocial Intervention Delivery (RAPID) trial builds on the feasibility and acceptability data for PREVAIL, SAFETEL and BrighterSide. As a multi-arm, multi-stage (MAMS) trial, RAPID uses an adaptive design that allows for these multiple interventions to be evaluated within one trial with pre-planned adaptations that allow for early selection of interventions that are promising, or the removal of interventions that are shown to be futile [29]. As such, the RAPID trial is an efficient approach to establishing the evidence base regarding the effectiveness of these interventions, within one single study, in comparison to a traditional randomised controlled trial (RCT) design [29]. Our focus on remote delivery of these established brief psychosocial interventions, if effective, would provide evidence for interventions that are sustainable and scalable solutions.

## Objectives

Our primary objective is to answer the question of which brief, remote psychosocial intervention for people with SMHPs who report recent suicidal ideation, or a suicide attempt is most clinically effective and cost-effective in preventing avoidable PHAs in comparison to TAU, and to determine the safety of the interventions.

Specific hypotheses are that, compared to TAU, our brief, remote interventions plus TAU will lead to:Reduction in psychiatric hospital admissions over 6 months (primary outcome)Reduction in psychiatric hospital admissions over 3 monthsReduction in suicidal ideation over 3 and 6 monthsImprovement in user-defined recovery and quality of life over 3 and 6 months

We also hypothesise that our interventions will be cost-effective over 6 months in comparison to TAU.

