## Statistical methods

### Statistical methods for primary and secondary outcomes

A detailed statistical analysis plan will be prepared and approved by the Trial Management Group (TMG), Data Monitoring Committee (DMC) and TSC prior to the interim analysis.

Descriptive statistics within each randomised group will be presented for baseline values. These will include counts and percentages for binary and categorical variables, and means and standard deviations, or medians with lower and upper quartiles, for continuous variables, along with minimum and maximum values and counts of missing values. There will be no tests of statistical significance or confidence intervals for differences between randomised groups on any baseline variable.

For the analysis of the primary outcome at both stages, we will use a generalised linear model that includes fixed effects for treatment, diagnosis and site using maximum likelihood estimation. For each pairwise comparison with TAU, we will report the difference in proportion of admissions as the estimate of treatment effect with 2-sided 95% confidence intervals and 1-sided *p* values.

Secondary outcomes with repeated measures at 3 and 6 months will be analysed at stage 2 only. These will be analysed with generalised linear mixed models (GLMMs) appropriate for the distribution of the outcome using maximum likelihood estimation. Fixed effects will be treatment, diagnosis, site, time and time*group interactions, with a random effect for participant. Treatment effect estimates will be reported as adjusted between-group mean differences in outcomes between the groups separately at 3 and 6 months with 2-sided 95% confidence intervals and 1-sided *p* values.

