## Health economics and cost-effectiveness methods

A within trial economic analysis will compare the net costs and health benefits of the included interventions (PREVAIL and SAFETEL) plus TAU to TAU alone over the 6-month trial follow-up, from the NHS and social care (costs) and patient (health benefits) perspective. The primary measure of health benefit will be quality-adjusted life-years (QALYs) estimated from the EQ-5D-5L and the utility tariffs recommended by NICE at the time of the analysis. Health and social care service use (self-report supplemented by electronic medical record review for psychiatric hospital admission data) and EQ-5D-5L data will be collected for each participant at baseline, 3 months and 6 months. Self-reported service use data will be collected using an Economic Patient Questionnaire (EPQ) developed and used by the applicants in previous trials in severe mental illness and adapted for this study. The UK literature recognises that issues with electronic routine data sources may result in self-reported data being the preferred option [46]. Due to the unfeasible nature of accessing and extracting full-service use from routine electronic data sources, the trial will collect psychiatric inpatient admissions from hospital record data (these are likely a key driver of costs in this population). With the rest being taken from the self-report questionnaire (EPQ), collected during interview. Items of resource use will be multiplied by published national health and social care costs (Department of Health Reference Costs; Unit Costs of Health and Social Care, PSSRU). The EPQ will be discussed and piloted with the SURG prior to being finalised for the start of the trial.

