Multiple imputation will be used to impute missing observations. The analyses will control for key baseline covariates or characteristics (demographic, socio-economic and clinical measures) identified from the published literature and supplemented with analysis of pooled baseline data. The cost and outcome effects will be bootstrapped to generate incremental cost-effectiveness ratios, cost-effectiveness acceptability curves and net benefit statistics. Cost-effectiveness acceptability curves (CEACs) will be plotted to summarise uncertainty associated with the ICER. To derive CEACs, the incremental cost and QALY (effect) estimates from the regression analyses will be bootstrapped to simulate the sample data of costs and QALY. The bootstrapped estimates of net QALYs will be revalued, using a range of ceiling ratios or willingness to pay thresholds (WTPT) to gain 1 QALY.

In the UK, there is no universally agreed cost-effectiveness threshold value. One commonly reported threshold is from NICE in England of approximately £20,000 to £30,000 per QALY [37]. However, there is a lack of consensus around the appropriate threshold [47, 48]. Therefore, the monetary value of simulated QALYs will be varied from £0 to £30,000 to reflect a range of hypothetical willingness to pay thresholds. As the analysis is comparing multiple options, a sensitivity analysis will adopt a fully incremental approach. Sensitivity analyses will also assess the choice of health benefit measure (QALYs calculated using ReQOL-10 as an alternative measure) and the impact of missing data (complete case versus imputed data). All economic analyses will be pre-specified in a Health Economic Analysis Plan (HEAP) to be agreed with the TSC and DMC. Reporting will be in line with the Consolidated Health Economic Evaluation Reporting Standards 2022 (CHEERS 2022) statement [49].

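### The primary objective asks which intervention is most effective and cost-effective, but the article plans only comparisons with TAU and leaves the three-option economic comparison to a sensitivity analysis

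*Protocol article*

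**What the plan says.** The Objectives section puts the primary objective as a question: "which brief, remote psychosocial intervention for people with SMHPs who report recent suicidal ideation, or a suicide attempt is most clinically effective and cost-effective". The same sentence names TAU as the reference, so the superlative reads in full as "most clinically effective and cost-effective in preventing avoidable PHAs in comparison to TAU". The hypotheses that follow are narrower: "Specific hypotheses are that, compared to TAU, our brief, remote interventions plus TAU will lead to" fewer admissions and improvements on the secondary outcomes. The economic hypothesis is that "our interventions will be cost-effective over 6 months in comparison to TAU". None is set between PREVAIL and SAFETEL.

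The section on statistical methods for primary and secondary outcomes fixes the clinical contrast: "For each pairwise comparison with TAU, we will report the difference in proportion of admissions as the estimate of treatment effect".

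The health economics section compares the net costs and benefits "of the included interventions (PREVAIL and SAFETEL) plus TAU to TAU alone over the 6-month trial follow-up". It plans incremental cost-effectiveness ratios, acceptability curves (CEACs) and net benefit statistics, with a QALY valued at £0 to £30,000. It then adds: "As the analysis is comparing multiple options, a sensitivity analysis will adopt a fully incremental approach". Full specification is left to a Health Economic Analysis Plan that is not shown.

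**The concern.** Asking which of two interventions has the larger effect against a shared control is asking for the difference between them, because (PREVAIL − TAU) − (SAFETEL − TAU) = PREVAIL − SAFETEL. The phrase about TAU in the objective names the reference group but does not remove the superlative. The objective and the hypotheses beneath it therefore ask different questions, and the stated clinical analysis answers only the second.

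The economic side matters more. PREVAIL plus TAU, SAFETEL plus TAU, and TAU alone are alternatives, and a commissioner chooses among all three. Two ratios against TAU can both fall below the threshold while the step from one intervention to the other does not. Acceptability curves drawn only against TAU give the probability that each arm beats TAU, not the probability that it is the best of three. The article's own reason for a fully incremental analysis, that several options are being compared, is a reason to put it in the main analysis.

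This is a planned situation. The maximum sample size is the case in which both arms continue, and the interim rules provide for a three-arm second stage. If the ranking method is not fixed beforehand, it may be chosen after the results are seen.

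**Working it through.** **1. What the sample size was built for.** Inputs from the Sample size and Sequence generation sections: 15% admissions on TAU, a difference of 7.5 points (so 7.5% on an active arm), one-sided alpha 0.025, power 90%, allocation 2:2:3, 5% loss. With unpooled variance and an active:TAU ratio of 2/3:

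n(TAU) = (1.960 + 1.2816)² × [0.15×0.85 + 0.075×0.925/(2/3)] / 0.075² = 432.6

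432.6 × 7/3 = 1009.3 evaluable, and 1009.3/0.95 = 1062.4. Rounding the arms up gives 433 + 289 + 289 = 1011, and 1011/0.95 = 1064. The stated 1064 is thus reproduced as a size for each active arm against TAU. No active-versus-active comparison enters it.

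**2. Precision of the head-to-head contrast.** If both arms continue there are about 289 evaluable per active arm. The article gives no expected PREVAIL-SAFETEL difference, so the rates below are assumptions. For a common rate p, the 95% half-width is 1.96 × √[2p(1−p)/289]:

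- p = 7.5%: 1.96 × √(2×0.069375/289) = 4.3 points
- p = 10%: 1.96 × √(2×0.09/289) = 4.9 points

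**3. Power of the same contrast.** Pooled two-proportion test, two-sided 5%, about 289 per arm:

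| Assumed rates | Power |
|---|---|
| 10% v 7.5% | 18.5% |
| 11.25% v 7.5% | 34% |
| 15% v 7.5% | 82% |

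For 90% power, 11.25% v 7.5% would need 1268 evaluable per arm and 10% v 7.5% would need 2683. The contrast can be estimated but not tested with useful power, unless one active arm does no better than TAU's expected 15%.

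**4. Why the two TAU contrasts do not supply that interval.** They share the TAU arm and so are correlated. At 15% on TAU and 7.5% on both active arms, each contrast has variance 0.069375/289 + 0.1275/433 = 0.000240 + 0.000294 = 0.000535. A reader who combines the two published intervals as if they were independent gets 1.96 × √(2×0.000535) = 6.4 points, against the correct 4.3. The right interval must come from the fitted model.

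**5. The economic contrast.** The documents give no incremental costs or QALYs, so this example is hypothetical. Against TAU, let PREVAIL be +£200 and +0.012 QALY, and SAFETEL +£500 and +0.020 QALY.

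- PREVAIL v TAU: 200/0.012 = £16,667 per QALY
- SAFETEL v TAU: 500/0.020 = £25,000 per QALY
- SAFETEL v PREVAIL: (500−200)/(0.020−0.012) = £37,500 per QALY

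Both ratios against TAU pass £30,000, but the step between the arms does not.

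The conflict depends on the figures. Holding the others fixed, at £30,000 it arises when SAFETEL's added cost lies between 200 + 0.008×30,000 = £440 and 0.020×30,000 = £600. At £20,000 it arises only between 200 + 0.008×20,000 = £360 and 0.020×20,000 = £400.

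**6. What the planned net benefit statistics already show.** In the same example:

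- At £30,000, PREVAIL: 0.012×30,000 − 200 = £160; SAFETEL: 0.020×30,000 − 500 = £100.
- At £20,000, PREVAIL: £240 − £200 = £40; SAFETEL: £400 − £500 = −£100.

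Mean net benefit against the common comparator ranks PREVAIL first at both values, in agreement with the incremental ratio. What it lacks is the joint uncertainty over three options.

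**The case against.** The strongest reply is that the objective names TAU as comparator in the same sentence, that every hypothesis is against TAU, and that the planned contrasts match those hypotheses. On this view the fault is loose wording, not a missing primary analysis. For the clinical half, that largely stands.

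It is also true that the arms can be ordered without any new analysis: both risk differences are measured against the same TAU group on the same scale, and net benefit is planned. A reader might infer that the trial cannot answer its primary objective. The documents do not support that. What is missing is a stated measure of uncertainty for the ranking.

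A reader might also infer that the main economic result will point to the wrong option. The hypothetical example does not show this, since planned net benefit picks the same arm as the incremental ratio. Only someone relying on the pairwise ratios alone would be misled. Nor is there evidence that the fully incremental analysis once had higher status and was downgraded; the article simply assigns it to sensitivity analysis.

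Finally, supplementary contrasts and economic detail are often left to the statistical and health economic analysis plans, which are not shown. The statement that no head-to-head estimate is planned is therefore a statement about this article only. The economic point does not rest on silence, because the article itself places the fully incremental analysis outside the base case.

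**Conclusion.** The point holds as a mismatch between a ranking objective and analyses framed against TAU. It is stronger on the economic side than on the clinical side. If both arms complete, the article offers point estimates that can be ordered, but no PREVAIL-SAFETEL difference with its interval. Its main economic comparison also does not commit to giving the probability that each of the three options is the most cost-effective.

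The head-to-head half-width of about 4.3 to 4.9 points rests on 289 evaluable per active arm and assumed rates of 7.5% to 10%. The £37,500 figure shows that a conflict is possible, not that it is likely. Nothing here implies an error in the sample size, the primary model or the interim rules. If one active arm is dropped at the interim, the head-to-head contrast at these numbers does not arise.

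**What to change.** 1. In the health economic analysis plan, make the fully incremental and net-benefit analysis across PREVAIL, SAFETEL and TAU the base case, with acceptability curves that show the probability of each option being the most cost-effective. Keep the pairwise ratios against TAU as supplementary.
2. In the statistical analysis plan, state that if both arms complete, the PREVAIL-SAFETEL risk difference with its 95% interval will be reported from the same primary model, labelled secondary and unpowered.
3. Reword the primary objective as the effect of each intervention against TAU, with ranking of the interventions as a secondary objective.

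The cost is wording in three documents, settled before unblinded final results are available. No new data or participants are needed, and the 1064 stands. The downside is a wide head-to-head interval, which should be reported as such and not read as evidence that the interventions are equivalent.
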